## Abstract

**Background:** Body dysmorphic disorder (BDD) is a relatively common mental disorder in adolescents and young adults, and is characterized by severe negative psychosocial consequences and high comorbidity as well as high mortality rates, mainly due to suicides. While patients in Germany have health insurance-financed access to evidence-based outpatient treatments, that is, cognitive-behavioral treatment (CBT), waiting lists are long. Furthermore, patients with BDD report diverse treatment barriers, primarily feelings of shame and the belief that they would be better off with treatments that would alter the perceived flaw(s). Given adolescents' and young adults' high affinity to electronic media, the accessibility of evidence-based care for this severe mental disorder could be improved by providing an internet-based therapist-guided CBT intervention.

**Methods:** In a two-arm randomized controlled trial (*N* = 40), adolescents and young adults (15–21 years) with a primary diagnosis of BDD based on a semi-structured clinical expert interview will be randomly allocated to an internet-based therapist-guided CBT intervention or a supportive internet-based therapy intervention. Assessments will take place at baseline, after mid-intervention (after 6 weeks), post-intervention, and at 4-week follow-up. The primary outcome is expert-rated BDD symptom severity at the primary endpoint post-intervention. Secondary outcomes include responder and remission rates based on expert rating, self-reported BDD symptoms, and psychosocial variables associated with BDD.

**Interventions:** The CBT-based intervention consists of six modules each comprising one to three sessions, which focus on psychoeducation, cognitive restructuring, work on self-esteem, exposure and ritual prevention, mirror retraining, and relapse prevention. A study therapist provides feedback after each session. The supportive therapy intervention consists of access to psychoeducational materials for the same 12-week period and at least one weekly supportive interaction with the study therapist.

**Conclusions:** This is the first study to examine the feasibility and efficacy of an internet-based therapist-guided CBT intervention in adolescents and young adults with BDD. It could be an important first step to increase accessibility of care in this age group and for this severe and debilitating mental disorder.

**Clinical Trial Registration:** German Register of Clinical Studies, DRKS00022055.

## Introduction

Body dysmorphic disorder (BDD) is characterized by one or more perceived flaws in one's body, which are not visible or appear minor to others [Diagnostic and Statistical Manual of Mental Disorders, DSM-5; (1)]. Appearance-related concerns can be delusional [i.e., individuals do not understand that their perception of their own appearance differs from reality; (2)], and there is evidence that BDD is linked to more delusional concerns in adolescence than in adulthood (3). These appearance-related concerns lead to negative emotions such as shame, anxiety, and depression (4). Moreover, they are accompanied by so-called safety behaviors, which are compulsive and mental rituals performed in order to check, fix, or improve the perceived flaw(s) (1). Further typical examples of safety behaviors include rumination processes (5) and avoidance of situations in which one is confronted with one's appearance flaws or in which the perceived flaws are exposed to others [e.g., looking at oneself in the mirror, going to a party; (6)].

Various studies hint at a similar phenomenological picture of BDD in adolescents and adults [e.g., (3, 7–14)]. BDD is highly debilitating, with case studies in children and adolescents showing that BDD sufferers achieve poorer school grades (15), give up leisure time activities (12), miss a lot of school (16) or even drop out of school (15), withdraw socially (12), and might even become housebound (14). Comorbidity is the rule rather than the exception (14), and the disorder is characterized by low self-esteem and low quality of life [e.g., (17, 18)] as well as high rates of suicidality (19). Thus, BDD is a severe mental disorder, for which adolescence is a critical age period given the mean age of onset at 16 years (20) and the particularly high prevalence rate of 3.6% among 15–21-year-olds (19). Against this background, the need for adequate treatment for this age group is clear.

Two meta-analyses summarized the growing number of randomized controlled treatment trials in BDD, and concluded that cognitive-behavioral therapy and a pharmacological intervention with selective serotonin reuptake inhibitors (SSRIs) represent first-choice treatments (21, 22). Evidence in adolescents is far more limited, although case studies also support the effectiveness of CBT (15, 23–25) and SSRIs (14–16, 24, 26). Two larger studies established the feasibility of CBT for BDD in adolescents (26) and the superiority of CBT over a control condition consisting of telephone monitoring and psychoeducational materials (27).

Despite being a therapy method that is financed by health care insurers, waiting lists for CBT for adolescents in Germany are long (28). Furthermore, BDD might still be relatively unknown to practitioners and appearance concerns might be mistaken for age-appropriate concerns that do not require therapeutic attention. Additionally, many patients with BDD are very reluctant to seek psychological treatment (29), mainly due to shame, but also the idea that a treatment that changes the perceived flaw (i.e., plastic surgery, dermatology) might be more suitable for their problem. Given the highly relevant role of body image in the transitions occurring during adolescence (30) and the long-term severe consequences for future development potentially caused by BDD, an adequate treatment of BDD in adolescence is indispensable but is hindered, among other things, by the aforementioned factors.

## Aims of the Study

The main aim of this study is to evaluate the efficacy of an internet-based therapist-guided CBT intervention (ImaginYouth) for reducing symptoms of BDD in adolescents and young adults (in the following named adolescents) and to evaluate its superiority over a supportive online therapy condition (SOT) from pre- to post-intervention. Furthermore, we aim to assess the stability of both efficacy and superiority to follow-up, and the acceptability and feasibility of the intervention format.

We hypothesize that the ImaginYouth intervention will reduce primary expert-rated BDD symptom severity from pre- to post-intervention. Further, we expect the reduction of primary BDD symptom severity to be greater in the ImaginYouth than in the SOT intervention group from pre- to post-intervention. Secondary analyses include the testing of the above-mentioned hypotheses regarding self-reported BDD-symptom severity and associated (comorbid) symptoms. Additionally, we hypothesize that the number of remitted patients and responders will be higher at post-intervention in the ImaginYouth than in the SOT intervention group. Moreover, we expect both the changes and differences between the conditions at post-intervention to be stable over the 4-week follow-up period, and thus hypothesize a significant symptom reduction from pre-intervention to follow-up and a larger symptom reduction from pre-intervention to follow-up in the ImaginYouth compared to the SOT intervention.

## Methods

### Design

A two-arm randomized controlled trial (RCT) will be conducted to evaluate the internet-based therapist- guided CBT intervention compared to a supportive online therapy intervention. After screening (t0), assessments will take place at baseline (t1), mid-intervention (t2), post-intervention (t3), and 4-week follow-up (t4). Figure 1 provides a detailed overview of the study design. The mid-intervention assessment will not be a focus of the main study and therefore of this protocol, but will be used to identify, for example, predictors and early responders in secondary exploratory analyses. All procedures involved in the study will be consistent with the generally accepted standards of ethical practice approved by the Osnabrück University ethics committee (Ethik-35/2018). The trial is registered in the German Register of Clinical Studies (Deutsches Register Klinischer Studien; DRKS00022055).

**Figure 1 F1:**
[figure not shown]
Flow chart illustrating the study design.

### Participants and Procedures

#### Inclusion and Exclusion Criteria

Inclusion criteria include age between 15 and 21 years, a primary diagnosis of BDD (comorbid diagnoses are allowed) established by the expert interview Body Dysmorphic Disorder Diagnostic Module for DSM-5 [BDDDM; (36)] after a previous sum score of ≥14 on the Body Dysmorphic Symptoms Inventory [BDDI as is in the Table; (37)] during the screening. Exclusion criteria current substance abuse, bipolar or psychotic episodes, suicidal intent and plans, current psychotherapy, cognitive limitations that would hinder work on the intervention, and/or a change in psychopharmacological medication in the last 2 months.

#### Recruitment

Recruitment will take place in mainly German-language countries (i.e., Germany, Austria, Switzerland) and will mostly be performed online through social media (e. g., Instagram, Facebook, YouTube), the study's website, and thematic websites. Furthermore, we will announce the start of the study (including in-depth information on the intervention and contact details) in a University press release, in newspapers, youth-specific magazines, student mailing lists/newsletters, student counseling centers or organizations, and to therapists affiliated with Osnabrück University.

#### Assessment of Eligibility and Randomization

After participants have contacted us by telephone, email or via our social media channels, they will be provided with a link to the online self-report screening (t0, in Unipark; EFS Survey, Questback GmbH, Cologne) through a self-chosen email address. If they fulfill the first inclusion criteria (age, BDDI as is in Table sum score ≥14, and no current psychotherapy), the diagnostician (a clinical psychologist in training) will contact them by email in order to make an appointment to (1) conduct the informed consent procedure and (2) complete the structured clinical interviews. The diagnostician is blind to the condition of the participant both at pre- and post-assessment. In case of crossover (i.e., a participation in ImaginYouth after having participated in SOT before) the ratings will not be blind anymore. The diagnostician will also provide the participants with detailed written information on the study procedure, our privacy policy and a note that it is possible to withdraw from the intervention at any time without facing any consequences. The informed consent procedure and the interviews will be conducted online using RedConnect (RED Medical Systems GmbH, Munich), the latter only after the informed consent form has been sent to the diagnostician by email. If the participants fulfill the remaining inclusion and exclusion criteria, they will then be randomized to one of the two intervention conditions by our external collaboration partners (AM and KS) who, from this point, will not be further involved in the study. A full randomization of the prospective 40 cases will be generated via a list randomizer (RANDOM.ORG, Randomness and Integrity Services Ltd, Dublin) by KS. Once randomization has been conducted, the second first-author (MS; study therapist in both conditions; clinical psychologist in training) will provide participants with a log-in for the intervention to which they have been allocated on the e-mental-health platform Minddistrict (Minddistrict, Berlin).

ImaginYouth consists of six modules comprising one to three sessions each. Each session can be completed in about 30–60 min and participants are advised to find a specific day on which they can take part in one session on the same day each week. If participants stick to their schedule, the intervention will last for 12 weeks. At the beginning of each session, participants are asked to report on their experiences with the last session and the homework in order to give them the opportunity to reflect on their BDD development. Furthermore, they have the chance to report on their current overall emotional state and to answer an open question on this week's particular life events. Sessions consist of psychoeducational materials on the topic being worked on (e.g., safety behaviors), including summarizing recap paragraphs and optional drop-down “Read more” sections to facilitate reading. This focus is due particularly to the diverse nature of the sample, especially in terms of age and cognitive abilities. Moreover, we included optional drop-down “Practical tips” sections for some of the exercises to provide further support if needed, as well as optional drop-down “Fun fact!” sections to enhance the overall experience of undergoing the session. Overall, attempts were made to tailor the sessions to the individual needs of the participants and to give the young participants a sense of autonomy and co-determination. The written content was enhanced by drawings that emphasize the information given as well as video and audio clips. Furthermore, participants are asked to complete mandatory exercises to apply the material to their own behavior and/or perception. The content and the exercises are accompanied by three teenage case descriptions (two girls, one boy) that are introduced in the first session. These serve as relatable examples by sharing their experiences with and everyday-life application of the current topic of the session and/or sharing their answers in the exercises to give participants a better idea of what they are being asked to do. Another connecting element of the sessions is the BDD model that is introduced in the second session. This model links to the current topic at the beginning of each session to explain the rationale for the proposed exercises, and aims to increase participants' motivation. At the end of each session, participants are asked to complete a short survey (see section Assessment and Data Management). Between sessions, participants work on homework that aims to facilitate transfer to the real-world setting (e.g., diaries, exposure exercises); this is often enhanced by “cheat sheets” summarizing the crucial content of the previous session. After each session, participants receive written feedback from the study therapist on the exercises and homework through the program's chat function. At the end of each module, participants can download a handout summarizing the crucial aspects of the module in order to create their personal BDD “toolbox.” After the completion of each session, further content is automatically released. New modules need to be released by the study therapist. While the sessions and the integrated chat can only be accessed *via* a web browser, the homework is also available on the complementary smartphone app. Detailed information on the number of sessions per module and content are illustrated in Table 1.

**Table 1 T1:** Description of modules, their number of sessions and content, and associated homework.

**Module**	**Number of sessions**	**Content**	**Homework**
Psychoeducation	2	Introduction to symptoms, prevalence and multifactorial development of BDD as well as therapy options; Introduction to the three accompanying case studies Bilal, Frieda and Birte	–
		Introduction to the BDD-model “The Vicious Circle of BDD”: development and maintenance of BDD; Optional information sheet on BDD for relatives and friends	Diary: Monitoring symptoms of BDD and time spend on preoccupation with flaw(s)
Automatic thoughts	2	Introduction to the link between thoughts and emotions; Identification of automatic dysfunctional thought patterns and errors in reasoning	Diary: Monitoring errors in judgement and associated feelings
		Questioning and replacing dysfunctional thoughts with more realistic, functional thoughts	Diary: Detecting, questioning and replacing errors in judgement with functional thoughts
Self-depreciating thoughts	1	Identification and remodeling of specific self-depreciating thoughts (“My inner critic”); Identification of positive character traits and values to enhance self-esteem	Interviewing three people on one's own positive character traits
Safety behavior	3	Problematization, identification und reduction of compulsive appearance-related rituals	Monitoring and reduction of two rituals
		Problematization and identification of avoidance behavior; Introduction to exposure therapy	Setting up an exposure plan; Exposure to one avoided situation
		Exposure therapy, continued: detecting typical obstacles and how to overcome them	Setting up an exposure plan; Exposure to three avoided situations
View in the mirror	3	Consequences of avoided or compulsive mirror checking; Associated selective attention processes and cognitive errors	Diary: Mirror checking protocol
		Introduction to a more functional view in the mirror and mirror exposure	Mirror exposure with pre-recorded audio instructions
		Mirror exposure, continued: refraining from safety behavior	Three mirror exposures with pre-recorded audio instructions
Future path/relapse prevention	1	Planning of further recovery steps; Relapse prevention: How to handle stressful events	-

#### Supportive Online Therapy Condition

A supportive therapy condition was chosen as the control condition, as this has proven to be feasible in BDD in adults (33) and in children and adolescents with depression or anxiety symptoms (38, 39). In the SOT condition, patients can read psychoeducational material on BDD for 12 weeks (symptoms, prevalence, development, maintenance, therapy options, case examples) that is identical to the psychoeducational reading material from the first module of the ImaginYouth condition, but without exercises to facilitate transfer to the patient's individual case or the identification of intervention targets. Through the program's messaging function, the control patients are contacted weekly (repeated in case of non-responding) by the study therapist. In this communication, the therapist asks about their current well-being as well as their experiences, thoughts, and emotions regarding BDD symptoms and how these influence participants' lives if participants do not bring up their own questions or concerns.

### Safety Management

Given the high suicidality in BDD (19), we aim to provide a thorough safety management in our study. First, potential participants with concrete suicidal intentions and plans identified during screening and/or diagnostic sessions will be excluded from participation and will be informed about potential places to seek treatment in their area of residence. During the intervention, we will have a weekly monitoring of suicidal ideation in place, which the study therapist has to consult prior to interaction with the patient. If suicidal ideation develops, a stepped-care plan will be set in motion, including anti-suicide contracts, a telephone call with the study therapist in which a stepped emergency plan is developed, a telephone call with the supervisor (AH; a clinical psychologist with expertise in treatment of BDD), and involvement of treatment providers in the patient's area of residence. In order to track the general development of all patients, a fortnightly supervision session will be held. The supervisor will be accessible for the study therapist during the whole project. For *post-hoc* analyses, we will also assess adverse events during and after the intervention (see measures) to assess its moderation of treatment effects.

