### Assessment and Data Management

Detailed self-reports will take place at screening (t0), baseline (t1) prior to randomization, mid-intervention (t2), post-intervention (t3), and 4-week follow-up (t4; see Figure 1 for a detailed overview). On a more regular basis, we will gather brief self-reports on suicidal intent and negative emotions (after each session) as well as on BDD and depressive symptoms (after each module). Self-reported data (t0 through t4) will be collected using the secure online-based assessment system Unipark (EFS Survey, Questback GmbH, Cologne). Expert interviews will be conducted over the internet at t1 and t3 *via* the secure online video conferencing platform RedConnect (RED Medical Systems GmbH, Munich).

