Item on suicidal thoughts and plans, beck-depression-inventory-II^Q^^,^^Post−session^	(66, 67)	Suicidal thoughts and plans	1	–	4-point scale from 0 (*I don't have any thoughts of harming myself*) to 3 (*I would kill myself if I could*)	–	x	x	x	x	x

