**Post−session:**
*after every completed session of the ImaginYouth condition and simultaneously in the Online supportive therapy condition/every week*;

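### Suicidality monitoring is promised weekly, but the ImaginYouth rating is tied to completing a session, and the two coincide only if a session is completed every week

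*Protocol article*

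**What the plan says.** The protocol article describes the timing of the suicidality rating in several places.

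- **Safety Management** sets a calendar frequency without distinguishing the arms: "During the intervention, we will have a weekly monitoring of suicidal ideation in place". The rating feeds the therapist's work, as something "which the study therapist has to consult prior to interaction with the patient".
- **Assessment and Data Management** gives an event trigger: "we will gather brief self-reports on suicidal intent and negative emotions (after each session".
- **Table 2** lists the instrument, "Item on suicidal thoughts and plans, beck-depression-inventory-II", as a single item with the post-session tag. The same row also marks it at t0, t1, t2, t3 and t4.
- **The post-session footnote to Table 2** defines the tag: "after every completed session of the ImaginYouth condition and simultaneously in the Online supportive therapy condition/every week".
- **ImaginYouth Condition** places the survey at the close of a session: "At the end of each session, participants are asked to complete a short survey". It refers the reader to Assessment and Data Management for details. The pace is a recommendation: "participants are advised to find a specific day on which they can take part in one session on the same day each week". The duration is conditional: "If participants stick to their schedule, the intervention will last for 12 weeks".

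The section on the supportive online therapy (SOT) condition says the therapist contacts those participants every week and tries again if they do not reply. In ImaginYouth, the therapist contact described is written feedback after each session.

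**The concern.** A calendar trigger and a completion trigger are different rules. They give the same data only for a participant who keeps exactly to the recommended pace. For anyone slower, the completion trigger yields fewer ratings than Safety Management promises. For anyone who stops, it yields none from that point until the next fixed assessment.

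A safety commitment is at stake. The protocol itself cites high suicidality in this disorder, and its stepped-care plan starts when suicidal ideation develops, which presupposes that it is detected. The therapist's check of the rating before an interaction is also weakened in ImaginYouth, because the rating and the described feedback both hang on a completed session. A participant who stalls sets off neither.

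**Working it through.** No statistical model is involved. The check is whether the two stated triggers can be the same schedule.

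**1. Planned schedule.** Sessions per module in Table 1: 2 + 2 + 1 + 3 + 3 + 1 = 12. At one session per week this gives 12 weeks, which reproduces the duration in the ImaginYouth Condition section. Under full adherence, a rating after each session is a weekly rating, and the passages agree.

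**2. Departure from the schedule.** Suppose a participant completes one session a week and stops after session *s*. Post-session ratings = *s*. Weeks of the 12 without one = 12 − *s*.

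| Stops after session | Post-session ratings | Weeks without one |
|---|---|---|
| 0 | 0 | 12 |
| 3 | 3 | 9 |
| 6 | 6 | 6 |
| 9 | 9 | 3 |
| 12 | 12 | 0 |

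**3. What the fixed assessments add.** Table 2 schedules the item at t2, t3 and t4 whatever the session progress. The Abstract places t2 after 6 weeks. The timing of t3 for a participant who has fallen behind is not stated; week 12 is assumed here. Someone who stops after session 1 (week 1) then has no scheduled rating for 6 − 1 = 5 weeks, one at t2, and none for a further 12 − 6 = 6 weeks until t3.

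**4. The Table 2 footnote.** The closing words on weekly collection can be read in two ways.

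- As the SOT schedule, which is the more natural reading. ImaginYouth is then rated by completed session and SOT by calendar.
- As a weekly schedule for both arms. The footnote then contains both triggers for ImaginYouth and still differs from Assessment and Data Management, which names only the session.

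In SOT, being rated at the same time as ImaginYouth and being rated every week also cease to be the same once ImaginYouth sessions slip. Neither reading leaves one trigger throughout.

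**5. How many are affected.** The Sample Size Calculation section uses 30% dropout to inflate the sample: 28 / (1 − 0.30) = 40. It describes loss from internet-based studies, not stopping of sessions by people who remain in the study, so the document gives no figure for the number affected.

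**The case against.** The strongest reply is that the passages agree on the schedule as planned, and that how late or silent users are prompted is operational detail which a condensed article leaves to the full protocol. The first half is right. The second would hold if the article were merely silent, but it states two triggers for one safety measure, and following the session trigger as written falls short of the weekly commitment.

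Other oversight exists. The therapist must release each new module, and fortnightly supervision follows all patients. Participants are therefore not unobserved, but neither step produces a suicidality rating.

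Several stronger readings are tempting, and the document does not support them:

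- **That stalled participants yield no monitoring data.** The item remains scheduled at t2, t3 and t4. The gap lies between those points.
- **That the footnote rules out weekly collection in ImaginYouth.** It is ambiguous.
- **That about 6 of 20 ImaginYouth participants (0.30 × 20) would be affected.** This treats study dropout as stopping of sessions. People who have left or no longer respond would not answer a self-report item under any trigger.
- **That the treatment comparison is compromised.** Statistical Methods plans pre/post and pre/follow-up comparisons and no between-arm analysis of post-session data. The suicidality and negative-emotion measures share the t1, t3 and t4 entries in both arms.
- **That those who stall are the ones deteriorating.** The document gives no evidence for this.

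**Conclusion.** The inconsistency is real and concerns a stated safety commitment. Weekly monitoring and monitoring by completed session coincide only if one of the 12 sessions is completed every week, which is advised but not enforced. Otherwise, an ImaginYouth participant has fewer ratings than promised, and one who stops has none between the fixed assessments. Only SOT has a described weekly contact repeated for non-responders.

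For an individual, the size ranges from no gap under full adherence to 12 weeks without a post-session rating if no session is completed, interrupted by t2 if it is answered. The gap lengths assume one session a week until stopping and t3 at week 12. The planned efficacy comparisons stand as they are. The conclusion rests on the more natural reading of the Table 2 footnote; on the other reading, the texts still differ and still need reconciling.

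**What to change.** Reconcile Safety Management, the ImaginYouth Condition section, Assessment and Data Management, and the post-session footnote to Table 2. The document should then state one consistent trigger for the suicidality item in each arm, and say what applies to a participant who has not completed a session. In the footnote, make clear which arm or arms the weekly wording covers. Which trigger to adopt is a clinical and safety decision for the sponsor; none is proposed here.

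The cost is a change of wording and, depending on the sponsor's choice, a scheduling change for a single-item questionnaire already in use. The article does not describe how that item is configured on the platform, so the technical effort cannot be judged from it. No change to the sample size or the planned analyses follows from this point.
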